### Data quality assurance

The follow-up survey of parents will be directly entered into an online program. To enhance the quality of this data, responses to most of the questions will be entered using checkboxes. Absence data collected on all children will be collected weekly by the school liaison research assistants and returned to the study co-ordinator. The study co-ordinator will check this data for invalid codes and dates before adding the data to the database.

### Sample size

The primary outcome in this C-RCT is the number of absence episodes due to illness. In the calculation of sample size for this outcome, adjustment needs to be

made for the clustered nature of the design. The variance inflation factor used to achieve this is determined from the average cluster size and the Intra-Cluster Correlation (ICC) [22]. A C-RCT investigating the effectiveness of handwashing promotion in primary school children in China, estimated an ICC of 0.15 for absence prevalence (*[name], personal communication 10 July 2007*). This estimate has been used in the following calculations. We have powered this trial to detect a 20% reduction in the rate of absence episodes due to illness between arms. If the rate of absence episodes due to illness at 20 weeks follow-up is 2.2 episodes per pupil in the control arm (equivalent to an average of 11 absences per 100 pupil-weeks; the average of 2006/07 winters in Otago/Southland), then a sample of 27 schools per arm, with an average of 50 pupils per school, will be sufficient to detect a 20% reduction in the rate, to 1.76 episodes per pupil per 20 weeks follow-up, with 80% power [23]. This assumes a significance level of 5%.

Allowing for 20% attrition in schools, we plan to initially recruit 34 schools per arm, providing outcome information on a total of 3400 pupils.

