## Abstract

**Background:** New Zealand has relatively high rates of morbidity and mortality from infectious disease compared with other OECD countries, with infectious disease being more prevalent in children compared with others in the population. Consequences of infectious disease in children may have significant economic and social impact beyond the direct effects of the disease on the health of the child; including absence from school, transmission of infectious disease to other pupils, staff, and family members, and time off work for parents/guardians. Reduction of the transmission of infectious disease between children at schools could be an effective way of reducing the community incidence of infectious disease. Alcohol based no-rinse hand sanitisers provide an alternative hand cleaning technology, for which there is some evidence that they may be effective in achieving this. However, very few studies have investigated the effectiveness of hand sanitisers, and importantly, the potential wider economic implications of this intervention have not been established.

**Aims:** The primary objective of this trial is to establish if the provision of hand sanitisers in primary schools in the South Island of New Zealand, in addition to an education session on hand hygiene, reduces the incidence rate of absence episodes due to illness in children. In addition, the trial will establish the cost-effectiveness and conduct a cost-benefit analysis of the intervention in this setting.

**Methods/Design:** A cluster randomised controlled trial will be undertaken to establish the effectiveness and cost-effectiveness of hand sanitisers. Sixty-eight primary schools will be recruited from three regions in the South Island of New Zealand. The schools will be randomised, within region, to receive hand sanitisers and an education session on hand hygiene, or an education session on hand hygiene alone. Fifty pupils from each school in years 1 to 6 (generally aged from 5 to 11 years) will be randomly selected for detailed follow-up about their illness absences, providing a total of 3400 pupils. In addition, absence information will be collected on all children from the school rolls. Investigators not involved in the running of the trial, outcome assessors, and the statistician will be blinded to the group allocation until the analysis is completed.

**Trial registration:** ACTRN12609000478213

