#### **Recruitment of follow-up children**

In each school, 50 children will be randomly selected from the school roll in February 2009 by a school liaison research assistant. For each school, a list of numbers between 1 and the total number of children in years 1 to 6 in that school will be randomly sorted. The school liaison research assistant will know what intervention group the school has been assigned to, but will be provided only with the first 50 numbers from the randomly sorted list and a printout of the current school roll by the school administrative staff. They will number the children on the list from 1 to the maximum number, and identify the children whose numbers correspond with the random numbers they have been provided with. They will record the name and class number of those children. The selected children's parents will be contacted by a letter and information sheet sent home via their child, to seek consent for follow-up, should those children be absent from school during terms 2 and 3.

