#### **Inclusion criteria**

Schools will be included if the following criteria are met:

- 1) There are at least 100 children of primary school age (school years 1 to 6; children will generally range in age from five to eleven years) at November 2008.
- 2) Schools are currently not using hand sanitiser products or are willing to not use hand sanitiser products for the period of the trial if they are randomised to the control group.
- 3) Schools are within the city boundaries of Christchurch, Dunedin, or Invercargill in NZ.
- 4) The principal of the school provides written consent for the school to participate in the trial, be randomised, and potentially receive the hand sanitisers.

Follow-up children will be included if the following criteria are met:

- 1) Their parents are able to read and understand spoken English to a level where they can read the study information sheet, complete the consent form, and respond to telephone interviews. This will be assessed from a question on the consent form.

- 2) They attend a year 1 to 6 class in one of the included schools, at the beginning of the second school term in 2009 (the end of April).

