##### **Secondary analyses**

We will use generalised estimating equations to estimate the effectiveness of the hand sanitisers using appropriate distribution and link functions for the secondary outcomes. As for the primary analysis, we will fit an exchangeable correlation structure and use robust variance estimation. All models will include the stratification variable.

For both the primary and secondary outcomes, we plan to also estimate the effectiveness of hand sanitisers adjusting for the potential confounder, school level

deprivation. Research suggests that social economic status may be associated with illness rates [27]. School level deprivation will be measured using the 'decile' assigned to each school by the Ministry of Education for funding purposes. It reflects the proportion of students who live in more deprived communities, using information from the Census on household income, occupation, household crowding, educational qualifications, and income support.

We plan to make no adjustment for multiple testing. All tests will be two-sided and carried out at the 5% level of significance. We will document any changes we make to the study design or statistical analysis plan, or both, in the trial report.

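### The Sample size section labels 3400 children drawn as 3400 with outcome data; its own 20% school loss leaves about 2700, and 50 per school is a maximum because consent comes after the draw.

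*Protocol*

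**What the plan says.** The Sample size section finds that 27 schools per arm, with a mean of 50 pupils in each, suffice for the target effect. It then allows for 20% of schools dropping out and concludes: "we plan to initially recruit 34 schools per arm, providing outcome information on a total of 3400 pupils".

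Other sections set out how the 50 arise:

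- **Recruitment of follow-up children:** the research assistant "will be provided only with the first 50 numbers from the randomly sorted list". Parents of the children so identified are then asked for consent.
- **Inclusion criteria:** parents must have enough English to "complete the consent form, and respond to telephone interviews". This is judged from a question on the consent form, so after the draw.
- **Exclusion criteria:** a principal may direct the study not to approach a family.
- **Timing and Ethical review:** post-absence interviews take place only with consenting parents.
- **Table 1:** the primary outcome comes from those interviews, in follow-up children only.
- **Analysis subsets:** children may change school and parents may withdraw; missing data are not imputed in the primary analysis.

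The Abstract also gives the figure, "providing a total of 3400 pupils", but attaches it to children randomly selected for follow-up.

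**The concern.** Three quantities are treated as one: children drawn, children enrolled, and children with primary outcome data. The Sample size sentence gives the first as if it were the third. It also counts pupils in all 68 schools while explaining that 68 are needed because some are expected to leave.

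The power calculation has the same gap at pupil level. It uses 50 analysed per school, yet 50 is the number drawn before exclusions and consent. Loss is provided for among schools but not among pupils. A reader who relies on the stated total and on 80% power would expect more children, and slightly more precision, than the design gives under its own attrition assumption.

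**Working it through.** **Inputs (Protocol, Sample size unless noted).** Control rate: "rate of absence episodes due to illness at 20 weeks follow-up is 2.2 episodes per pupil in the control arm". Target: a 20% "reduction in the rate, to 1.76 episodes per pupil per 20 weeks follow-up, with 80% power". ICC 0.15; 50 pupils per school; 20% school attrition. Significance level 5%, two-sided (Secondary analyses: "All tests will be two-sided and carried out at the 5% level of significance"). The consent and retention rate is not given, so the values below are assumptions.

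**Step 1: reproduce the plan's figures.**

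- Pupils per arm without clustering: (1.960 + 0.842)² x (1/2.2 + 1/1.76) / (ln 0.8)² = 7.849 x 1.0227 / 0.04979 = 161.2. Working on the rate difference gives 160.5.
- Design effect: 1 + (50 - 1) x 0.15 = 8.35.
- Schools per arm: 161.2 x 8.35 / 50 = 26.9 (26.8 from 160.5), rounded up to 27.
- Attrition: 27 / 0.8 = 33.75, rounded up to 34.
- Total: 34 x 2 x 50 = 3400.

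All stated figures reproduce, and 3400 contains no loss at either level. The Protocol cites a Poisson regression method without writing out its formula. A version using the null variance gives 24.8 schools per arm, which does not match 27, so the version above is used.

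**Step 2: apply the plan's own school loss.** 27 x 2 x 50 = 2700 (or 0.8 x 3400 = 2720). That is 700 below 3400, or 21%, with every selected child still included.

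**Step 3: let the cluster size m fall below 50.** For k schools per arm,

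power = Φ( 0.2231 / √[ 1.0227 x (1 + (m - 1) x 0.15) / (k m) ] - 1.96 ).

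At k = 27, m = 50 the root is √(1.0227 x 8.35 / 1350) = 0.0795, and 0.2231 / 0.0795 - 1.96 = 0.85, so power is 80.1%.

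| Assumed share of the 50 with data | m | Pupils, 27 per arm | Power, 27 per arm | Pupils, 34 per arm | Power, 34 per arm |
|---|---|---|---|---|---|
| 100% | 50 | 2700 | 80.1% | 3400 | 88.3% |
| 80% | 40 | 2160 | 79.1% | 2720 | 87.5% |
| 60% | 30 | 1620 | 77.5% | 2040 | 86.1% |
| 50% | 25 | 1350 | 76.2% | 1700 | 85.1% |

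**Step 4: schools needed to keep 80%, before school attrition.** 28 per arm at m = 40, 29 at m = 30 and 30 at m = 25. With an ICC of 0.15 the number of schools dominates, so halving the cluster size raises the requirement only from 27 to 30.

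**The case against.** The best defence is that 20% is a contingency and 3400 a recruitment target. If fewer schools leave, more than 2700 children remain, and the Analysis subsets section expects little attrition for the primary outcome. This stands in part: 2700 is the figure under the stated attrition, not an upper limit. It does not rescue the wording, because the sentence speaks of outcome data and not of children approached.

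A second defence is that school staff may supply the reason for an absence when parents cannot be reached. That covers failed contact with enrolled families, not parents who never consent. The roll data on all children measure absence for any reason, so they do not supply the primary outcome either.

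It is also fair that the lack of replacements is read from silence, and that limiting the assistant to 50 numbers may be a safeguard, since that person knows the school's allocation. The English criterion overlaps with consent and should not be counted as a wholly separate loss. Still, no oversampling or replacement is described, so 50 remains the most the written procedure can yield.

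Four stronger inferences are not supported:

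- *The trial is seriously underpowered, or its size out of reach.* The table shows otherwise. With 30 schools per arm (4 of 34 lost, 12%) and 50% consent, power is still 80.4%.
- *The Abstract repeats the error.* It describes 3400 as children selected, which is accurate.
- *Rarer respiratory and gastrointestinal outcomes suffer most from smaller clusters.* On this formula, going from m = 50 to 25 multiplies the variance by (4.6/25) / (8.35/50) = 1.10 whatever the rate. The Protocol gives no rates or ICCs for these outcomes that would show otherwise.
- *Topping up to 50 consenters is an easy cure.* An assistant who knows the allocation would be adding children, which risks selection that differs by arm. Each added child also brings further interviews.

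**Conclusion.** The point holds as a mislabelled total and a missing pupil-level allowance. The school numbers are right. Under the plan's own school attrition, about 2700 pupils would have outcome data with full participation, and fewer after exclusions and non-consent.

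The stated 80% power was met with almost no margin (26.9 rounded to 27), so on the formula that reproduces 27, losing 10% or more of the pupils together with the full school loss takes it below target. The shortfall is about 1 percentage point at 80% consent, under 3 at 60% and about 4 at 50%. These sizes take the Protocol's rates and ICC as given and rest on assumed consent rates. On the null-variance version the need is 26.5 schools per arm at m = 30 and 27.3 at m = 25, so the effect would be smaller still.

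**What to change.** In the Sample size section, replace the closing statement with one that separates the quantities:

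- 3400 children (68 schools x 50) will be selected and their parents invited.
- If 20% of schools are lost and every selected child takes part, about 2700 will have outcome data.
- With an assumed consent and retention rate of c, the mean cluster size is 50c, and power at 27 schools per arm is the value for that size. For example, c = 0.8 gives 40 per school, 2160 pupils and 79.1%.

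The value of c is for the investigators to choose and justify; the Protocol offers none. The Abstract needs no change, and neither do the figures of 27 and 34 schools. The cost is a few sentences and a slightly lower stated power, with no change to conduct.

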#### **Effectiveness analyses**

##### **Analysis subsets**

The principal of intention-to-treat (ITT) is the appropriate strategy to be used in the primary analysis of the data in this C-RCT for two key reasons. It has the advantage of providing an unbiased estimate of intervention effect because it maintains the balance in prognostic factors between intervention groups, brought about through randomisation. In addition, it allows for non-compliance of hand sanitiser use, therefore providing an estimate of intervention effect which is more reflective of what would occur should the hand sanitisers be implemented in schools [24,25].

Requirements of an ideal ITT analysis include full compliance with the randomised intervention, no missing responses, and follow-up on all participants [24]. In a C-RCT, non-adherence to the intervention and loss to follow-up are more complex than in an individually RCT, since these can occur at multiple levels. In this trial, at the school level, schools in the intervention group may cease using the hand sanitisers while schools in the control group may commence using hand sanitisers, and in addition, schools may withdraw. At the level of the child, there will be non-adherence to the intervention, children may move schools, and parents of 'follow-up children' may withdraw.

We plan to implement procedures to maintain compliance and minimise loss to follow-up. While we expect there will be some attrition, we do not expect this to be large for the primary outcome, or the outcomes

collected on all children. For the former, if we are unable to contact the parents' of the 'follow-up children' to ascertain why they were absent, we may be able to determine the reason for the absence from the school administrative staff. For the latter, this data will be collected from the school roll where possible. Therefore, as our primary analysis, we plan to present a modified ITT analysis, where we will analyse participants as they have been randomised, regardless of the intervention they received, but will not impute missing data. As a second approach, we plan to identify potential predictors of missingness through modelling, and include these predictors in the primary analysis model.

A secondary per-protocol analysis will be undertaken where we will only include schools which complied with their allocated intervention. For the intervention group, we will define schools as complying if they used at least 45 ml per child of hand sanitiser solution over the study period. This usage equates to using the hand sanitiser at least once per day.

##### **Descriptive analyses at baseline**

Descriptive statistics will be presented by intervention group at baseline to compare the comparability of the groups and to provide a description of the population. Summary statistics of demographic and potential confounding variables will be presented.

##### **Primary analysis**

We will estimate the effectiveness of the hand sanitisers on the number of absence episodes due to any illness with marginal modelling using a generalised estimating equation. This will appropriately account for correlation that will occur between children within the same school. We plan to fit an exchangeable correlation structure, where responses from the same the same school are assumed to be equally correlated [26]. In addition, we will use robust variance estimation which will provide valid standard errors even if the within-school correlation structure has been mis-specified [18]. For this outcome, a negative binomial distribution and link function will be used. This model will include the stratification variable geographical area.

##### **Secondary analyses**

We will use generalised estimating equations to estimate the effectiveness of the hand sanitisers using appropriate distribution and link functions for the secondary outcomes. As for the primary analysis, we will fit an exchangeable correlation structure and use robust variance estimation. All models will include the stratification variable.

For both the primary and secondary outcomes, we plan to also estimate the effectiveness of hand sanitisers adjusting for the potential confounder, school level

deprivation. Research suggests that social economic status may be associated with illness rates [27]. School level deprivation will be measured using the 'decile' assigned to each school by the Ministry of Education for funding purposes. It reflects the proportion of students who live in more deprived communities, using information from the Census on household income, occupation, household crowding, educational qualifications, and income support.

We plan to make no adjustment for multiple testing. All tests will be two-sided and carried out at the 5% level of significance. We will document any changes we make to the study design or statistical analysis plan, or both, in the trial report.

#### **Economic evaluation**

One of the more challenging aspects of this study is determining the economic cost associated with children's illness and subsequent absence from school. Broadly speaking there are two basic approaches we can take to measuring these costs and we will employ both. By capturing individuals' employment circumstances and the amount of time all family members' work time is missed as a result of the illness, we can take a Human Capital approach to estimating the economic impact of the children's illness. While the Human Capital approach is widely used in economic evaluation, its use is particularly limited here as families in which no work time is lost have no cost associated with that illness. As such, we also adopt a WTP approach, asking parents to assign a value to the cost of the illness. Following the techniques described by Liu et al [28], this is done by asking parents to arrive at a figure that they would be prepared to pay to purchase a hypothetical medication that would keep their child from acquiring the same illness (i.e. same symptoms, severity and duration). The main advantage of this approach is that it allows respondents to place whatever values they deem appropriate in terms of inconvenience, lost work time and the pain and suffering of their children.

There is no clear indication in the literature in terms of the best approach to be used to arrive at a WTP figure. To avoid the risk of systematically under or over estimating WTP, each interviewer is randomly assigned an approach for each new respondent. The first approach simply asks the respondent to arrive at a figure on their own. The second approach starts with very low values and works upwards in pre-determined increments. The third approach starts with a very high value and works downwards in pre-determined increments. The questioning sequence used is available in Additional file 4 - Willingness-to-pay questioning sequence.

The analysis will provide a direct comparison between the Human Capital and the WTP approaches. We will also decompose the costs across various sub-populations

(i.e. different family structures, ethnic groups, low and high socio-economic status) to determine the extent to which the economic effect of children's illness has a different impact on different types of families, of people with different levels of extended family support and across socio-economic groups (measured by income, education and employment status).

A second objective is to examine the extent to which WTP is affected by the way the question is asked. We believe this will make an important methodological contribution in the collection of WTP data.

#### **Publication policy**

The principal investigator (PP) will ensure that the results from this trial are published regardless of the outcome. Reporting of the trial will adhere to the relevant, and most up-to-date, CONSORT statements at the time of submission [29-31].

#### **Ethical review**

The New Zealand Multi-Region Health and Disability Ethics Committee provided approval for the trial on 13 March 2009 (MEC/09/01/005).

C-RCTs offer additional ethical complexity compared to individually randomised participant trials [32-34], particularly concerning informed consent of individuals. In this trial, the school principals will act as the "gatekeepers"; providing written consent for the school to participate in the trial, be randomised, and potentially receive the hand sanitisers. Parents of all children in the schools allocated to the hand sanitiser group will be contacted with an information sheet explaining the study and informed that hand sanitisers will be fitted in each classroom in their child's school. Parents will be informed that they can opt their child out of using the hand sanitiser at any stage throughout the trial. Parents of the randomly selected sub-sample of children (including children in the intervention and control groups) will be asked to provide written informed consent for the researchers to conduct post-absence interviews with them.

Anonymised data on absences from all children will be collected from the school rolls. Consent for this data collection will not be obtained from parents. Parents of the children in the intervention group will be informed that this data will be collected, through the information sheet described above. Parents of the children in the control group will not be informed of the anonymised data collection.

